### **7.3.2 Blood samples**

Peripheral blood samples to allow analysis of JAK2-V617F, CALR 5bp insertion (exon 9) and CALR 52bp deletion (exon 9) mutant allele burden should be collected in lithium heparin tubes and sent to Cambridge at baseline, 12 weeks and 24 weeks.

At baseline and 24 weeks, 60 ml of blood will be collected to allow comparison of oestrogen receptor signalling in progenitor cells.

At week 12, 30 ml blood should be obtained. The remainder of the blood not required to assess allele burden will be banked at CBSB.

The level of allele burden at 12 weeks for each patient will be provided to sites in time to inform a decision about tamoxifen dose escalation and treatment continuation beyond 24 weeks. It is not possible to provide these in real time and therefore they cannot be used as a guide for patient management.

For responder patients continuing treatment beyond 24 weeks and 36 weeks, 60 ml of peripheral blood in lithium heparin tubes should be sent to the CBSB to reassess allele burden at 36 weeks and 48 weeks, respectively. The level of allele burden observed at 24, 36 and 48 weeks for each patient will also be provided to sites to inform a decision about further tamoxifen treatment continuation. It is not possible to provide these in real time and therefore they cannot be used as a guide for patient management.

In the unlikely event that a trial blood sample is lost, damaged or mishandled so it cannot be analysed, the trial office will request another sample.

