### 7.8 Patient Follow Up

All patients will be followed up until 28 days after the last administration of tamoxifen. This applies if treatment is stopped at 24 weeks, or 28 days after the last treatment if the patient continues beyond 24 weeks. Patients stopping trial treatment early will continue to be followed up for the trial outcomes as per protocol schedule unless the patient specifically withdraws consent.

If patients discontinue study drug prior to 24 weeks, collection of blood samples for central assessment of mutant allele burden should continue to be taken at the protocol specified time points providing the patient received at least 2 months of tamoxifen treatment, and the time point is <3 months from the last date of trial treatment.

Patients continuing trial treatment beyond 24 weeks will have their mutant allele burden reassessed at 36 weeks. Patients continuing trial treatment beyond 36 weeks will have their mutant allele burden reassessed at 48 weeks.

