## 12.2 Analysis of Outcome Measures

### 12.2.1 Primary outcome measure

Analysis of the primary outcome will be completed on an intention to treat basis. The proportion of patients who have achieved the primary outcome of a reduction in allele burden of  $\geq 50\%$  will be presented. Given 3 or more patients have achieved this level of reduction in allele burden the treatment will be deemed to show evidence of activity and will warrant further investigation. Patients who die or are lost to follow up prior to the primary end point of 24 weeks will be classed as non-responders.

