### 12.2.3 Exploratory outcome measure

All exploratory outcomes will be analysed in a descriptive manner on an intention to treat basis with no formal hypothesis testing taking place.

- Change in allele burden at 12 and 24 weeks compared to baseline will be obtained following analysis of peripheral blood at University of Cambridge and will be presented as the median change from baseline at each time point with the interquartile ranges.
- Proportion of patients showing a decrease in requirement for cytoreduction therapy at 24 weeks compared to baseline will be presented as the number and percentage of patients who have a decrease in treatment dose. Patients who die or are lost to follow up prior to week 24 will be classed as non-responders.
- Proportion of patients showing a decrease in allele burden of  $\geq 50\%$  at 36 and 48 weeks compared to baseline will also be obtained following analysis of peripheral blood at University of Cambridge. Counts and percentages of patients who have achieved the reduction at 36 and 48 weeks will be presented. This will only be presented for patients who remain on treatment post week 24 and are assessed at week 36 and week 48, respectively.
- 
- Duration of reduction in the peripheral blood JAK2-V617F, CALR 5bp insertion (exon 9), or CALR 52bp deletion (exon 9) mutant allele burden, defined as time between visits from first

observed reduction of  $\geq 50\%$  until the visit at which reduction from baseline becomes  $< 25\%$  or the last visit before the patient dies, will be tabulated.

- Expression (RNAseq), DNA-protein interaction (ChIPSeq) and methylation studies will be analysed and presented by the University of Cambridge.

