### 12.5 Planned Final Analyses

The main analysis of the trial will take place once the final patient reaches all trial endpoint at week 48 or discontinues trial treatment, whatever happens first.

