### 12.6 Power Calculations

A single stage A'herns design is used to give evidence of activity for the treatment. It is anticipated that no patients on the current treatment will achieve a reduction of  $\geq 50\%$  in allele burden. Given this, if 10% of the patients in this trial were to achieve the required reduction then the treatment would warrant further investigation in a randomised trial. If just 2% of the patients in the trial were to achieve the required level of reduction then the treatment would not be deemed to show any activity that would warrant further investigation. Based on these levels of acceptability and given a one sided alpha of 0.1 and power of 80%, 42 patients would be required for the study. If 3 or more of the recruited patients were to achieve a reduction in allele burden of  $\geq 50\%$  then it can be concluded that the treatment shows a signal of activity and the treatment warrants further investigation in a randomised trial. Patients who die or are lost to follow up prior to the response time point of 24 weeks will be classed as non-responders.

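### The 36/48-week response rate is labelled intention to treat but computed on a selected on-treatment group, and the main analysis can be triggered before the final patient's data are complete

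*Combined protocol and SAP*

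**What the plan says.** **36/48-week response.** Section 12.2.3 opens with "All exploratory outcomes will be analysed in a descriptive manner on an intention to treat basis". Its bullet on the 36- and 48-week response then restricts the denominator: "This will only be presented for patients who remain on treatment post week 24 and are assessed at week 36", with the same condition for week 48. Section 7.1 leaves treatment after week 24 to the investigator, for patients receiving benefit. It encourages continuation, without requiring it, where at least one of three criteria is met; the first is a ≥25% reduction in allele burden.

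**Who is sampled.** Section 7.3.2 describes the later samples as "For responder patients continuing treatment beyond 24 weeks and 36 weeks". Section 7.8 says: "Patients continuing trial treatment beyond 24 weeks will have their mutant allele burden reassessed at 36 weeks". Footnote 8 of the Schedule of Events and section 3 agree with section 7.8.

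**Week-24 non-response.** Section 12.2.1 states: "Patients who die or are lost to follow up prior to the primary end point of 24 weeks will be classed as non-responders". Section 12.6 repeats this. Section 7.8 keeps patients who stop early in follow-up, but takes their allele-burden samples only "providing the patient received at least 2 months of tamoxifen treatment" and only if the time point is less than 3 months after the last dose.

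**Timing.** Under section 12.5 the main analysis takes place "once the final patient reaches all trial endpoint at week 48 or discontinues trial treatment, whatever happens first". Section 8.1.3 collects adverse events to 28 days after the last treatment.

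**The concern.** The first two statements in section 12.2.3 cannot both hold. A proportion restricted to patients who stayed on treatment and were sampled is not an intention-to-treat proportion. Since staying on treatment depends in part on the variable being summarised, the percentage can exceed the week-24 percentage with no further drug effect. A reader who sees the intention-to-treat label would not expect that.

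Followed literally, section 12.5 can start the main analysis while safety data, and possibly a primary-endpoint sample, are still due for the final patient. Finally, a patient who stops very early is neither dead nor lost to follow-up and has no week-24 sample, so the text assigns that patient no primary outcome.

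**Working it through.** **Design figure.** Section 12.6 states "given a one sided alpha of 0.1 and power of 80%, 42 patients would be required for the study", with an uninteresting rate of 2%, a rate of interest of 10%, and 3 or more responders as the rule. By the exact binomial, P(X ≥ 3 | n = 42, p = 0.02) = 0.0515 and P(X ≥ 3 | n = 42, p = 0.10) = 0.805. This is the smallest design that meets both limits: n = 41 gives power 0.791. The sample size is reproduced and is not in question.

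**1. Denominator at 36/48 weeks.** The number continuing is not given, so it is assumed here. Rate = responders / denominator, with 3 responders:

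| Denominator | Rate |
|---|---|
| 10 continuing (assumed) | 3/10 = 30% |
| 20 continuing (assumed) | 3/20 = 15% |
| 30 continuing (assumed) | 3/30 = 10% |
| 42 registered (planned) | 3/42 = 7.1% |

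Over these assumptions the gap runs from 10 − 7.1 = 2.9 to 30 − 7.1 = 22.9 percentage points. The conflict over sampling adds to this. Section 7.3.2 does not define responder. If it means a ≥50% fall at week 24, the denominator would hold only patients who had already met the endpoint, and the figure would describe persistence of response. If all continuing patients are sampled, it describes response on continued treatment.

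**2. Analysis trigger.** Take a final patient who stops at week 16:
- The trigger in section 12.5 is met at week 16.
- The adverse event window closes 28 days later, at week 20.
- Exposure is 16 weeks, more than 2 months, and week 24 is 8 weeks after the last dose, less than 3 months. Section 7.8 therefore still requires the week-24 sample, which section 12.1.1 accepts up to week 28.

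The trigger thus falls 4 weeks before the safety window closes and 8 weeks before the nominal primary-endpoint sample. This holds on either reading of final patient.

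If final patient means last registered, other patients are affected too. Assume uniform accrual of 42 over 28 months: 42/28 = 1.5 per month, or 1.5/4.348 = 0.345 per week. If the last registrant stops at week w, about 0.345 × (24 − w) others have not reached week 24:
- w = 4: 0.345 × 20 = 6.9, about 7 patients.
- w = 12: 0.345 × 12 = 4.1, about 4 patients.

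**3. Early stoppers without a sample.** With 3 months taken as 13 weeks, the recency condition at nominal week 24 fails for stops before about week 24 − 13 = 11. If the earliest accepted sample (week 20) counts as the time point, recency reaches back to week 20 − 13 = 7, and the 2-month exposure condition, about week 9, binds instead. The gap therefore covers stops before about week 9 to 11. It affects the percentage: 4 responders read 4/42 = 9.5%, but 4/38 = 10.5% if four unsampled patients are left out and 4/32 = 12.5% if ten are (both numbers assumed). An unsampled patient cannot add to the count of responders.

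**The case against.** The 36/48-week item is exploratory, descriptive and untested, and its restriction is stated openly with counts alongside percentages. Treatment after week 24 is optional, and samples are planned only for patients who continue, so an on-treatment summary is all that can be observed. That stands. It argues for changing the label, and against making a headline rate in which patients never due a sample are scored as failures; a patient with a ≥50% fall at week 24 who stopped by choice would then count as a failure.

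A reader might infer that selection alone will make the later rates far better than the week-24 rate. The documents do not support this. They give no number continuing, and continuation can also rest on haematological response or reduced need for cytoreduction. It is not mandated, and section 7.3.2 says the allele-burden results are not available in real time.

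A reader might also infer that everyone who stops tamoxifen escapes the non-responder rule. Under section 7.8, those with enough exposure and a recent enough last dose are sampled and classified on the result. Moreover, the primary analysis is by intention to treat, and section 12.6 counts responders among recruited patients, so the intended denominator can fairly be inferred.

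On timing, final patient may naturally mean the last patient still on trial. The exposure is then one patient's 28-day window and possibly one week-24 sample. Section 12.2.1 also gives no basis for classifying living patients in follow-up who have not reached week 24. That narrows the point, but section 12.5 as worded still comes too early.

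**Conclusion.** The point holds at the level of wording, in three parts of unequal weight. The intention-to-treat label on the 36/48-week rate contradicts the restriction in the same section, and the sampling rule for that rate is inconsistent between sections. The difference from an all-registered percentage is 2.9 to 22.9 points for 3 responders and an assumed 30 down to 10 continuing patients; the true size is unknown. Section 12.5 can start the main analysis before the final patient's safety window and a required week-24 sample. The figure of about 7 other patients short of week 24 needs three further conditions: final patient means last registered, that patient stops at week 4, and accrual is uniform.

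The gap for early stoppers is a minor clarification. It leaves the reported percentage open but does not change the decision, provided the count of 3 or more in sections 12.2.1 and 12.6 governs rather than the 10% wording in section 1.2.2. Sample size, alpha and power are unaffected by these findings.

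**What to change.** - **Section 12.2.3:** remove the intention-to-treat label for the 36/48-week item, describe it as an on-treatment summary of a selected group, and show the number of responders against all registered patients (42 planned) beside it.
- **Sections 7.3.2 and 7.8, with Schedule of Events footnote 8:** reconcile these so that one rule states which continuing patients are sampled.
- **Section 12.5:** run the main analysis only after every patient has passed the week-24 window (+4 weeks) and has reached week 48 or 28 days after the last dose, as applicable.
- **Sections 12.2.1 and 12.6:** state that any registered patient without a central week-24 result, for whatever reason, is a non-responder, and that the denominator is all registered patients.

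The cost is a wording amendment, with no new patients. The downside is a short delay to the main analysis: in the week-16 example, up to 28 − 16 = 12 weeks.

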### 12.3 Planned Sub Group Analyses

Due to the lack of statistical power for subgroup analyses in this early phase II trial, results provided will be exploratory only. Therefore, results should not be over interpreted and instead used as a guide for further subgroup analyses in a larger phase III setting. Subgroups to be studied include:

- Results by mutation type (JAK2-V617F, CALR 5bp insertion (exon 9), CALR 52bp deletion (exon 9))
- Primary disease (ET, PV, MF)
- Oestrogen receptor data
- Sex

### 12.4 Planned Interim Analysis

Accumulating data will be analysed and presented on a regular basis (6 monthly) to an independent TSC for monitoring of safety and futility. Analysis will also be performed and presented to the TSC if 7 or more patients out of the first 21 patients registered are deemed to not have tolerated treatment. A patient is classed as not being able to tolerate treatment if they discontinue treatment due to:

- Unacceptable toxicity, defined as:
  - Grade 3-4 adverse event considered related to tamoxifen
  - Persisting grade 1-2 adverse events considered related to tamoxifen lasting more than 14 days and that do not resolve within 4 weeks of reducing tamoxifen to 10 mg od
- Thrombotic event of any grade

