## **7.4 Dose Modifications**

Unless prevented by persistent side effects greater than grade 1, dose escalations to 40 mg tamoxifen od are encouraged, but not mandated, for patients either not showing a reduction in allele burden  $\geq 50\%$  or not showing an improvement of haematological response at 12 weeks compared to baseline.

Dose reductions to 10 mg tamoxifen od are allowed, but not mandated, for patients that develop mild/moderate side effects (grades 1-2) except for those experiencing thrombotic events, which will mandate permanent treatment discontinuation regardless of grade.

Dose modifications are only permitted on an individual basis at the discretion of the Chief Investigator/Clinical Coordinator. Please contact the Trials Office to discuss any dose changes. All changes must be recorded on the CRF.

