### 7.9 Patient Withdrawal

In the event of discontinuation of study treatment, e.g. unacceptable toxicity or patient choice, full details of the reason/s for discontinuation should be recorded on the CRF.

All patients, including non-compliant subjects, should be followed up according to the protocol schedule unless they withdraw specific consent.

In the event of a patient's decision to withdraw from the trial, the Investigator should ascertain from which aspects of the trial the patient wishes to withdraw and record the details on the appropriate CRF. All information and blood/bone marrow samples collected up until the point of retraction will be retained and analysed. If a patient chooses to withdraw from treatment only, the patient should discontinue treatment and continue to be assessed in accordance with the protocol. If a patient wishes to withdraw from the trial (i.e. including trial specific assessments), but is willing for further data to be supplied to the Trials Office, then further routine 'follow-up' data (e.g. toxicity data) will continue to be supplied by the Investigator to the Trials Office.

Patients who stop treatment due to adverse experiences (clinical or laboratory) will be treated and followed according to accepted medical practice. All pertinent information concerning the outcome of such treatment must be recorded in the CRF.

The following are justifiable reasons for the Investigator to stop study treatment:

- Unforeseen events: any event which in the judgement of the Investigator makes further treatment inadvisable
- Serious violation of the trial protocol (including persistent patient non-attendance and persistent non-compliance)
- Stopping by the Investigator for clinical reasons not related to the study drug treatment

Patients must stop study treatment in the event of:

- Unacceptable toxicity, defined as:
  - Grade 3-4 adverse event considered related to the trial IMP
  - Persisting grade 1-2 adverse events considered related to the trial IMP lasting more than 14 days and that do not resolve within 4 weeks of reducing tamoxifen to 10 mg od
- Thrombotic event of any grade
- SAE requiring permanent discontinuation of treatment
- Transformation to MDS or AML

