### 8.2.5 Trial Steering Committee

The independent Trial Steering Committee (TSC) will review all SAEs.

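### The 7-of-21 tolerability trigger in 12.4 counts a persistent related grade 1-2 stop only after a failed reduction to 10 mg, a step that 7.4 makes optional

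*Combined protocol and SAP*

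**What the plan says.** Section 12.4 (Planned Interim Analysis) sets the trigger at 7 or more of the first 21 registered patients. It defines the count this way: "A patient is classed as not being able to tolerate treatment if they discontinue treatment due to" one of three things.

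- A grade 3-4 adverse event related to tamoxifen.
- A related grade 1-2 adverse event that persists for more than 14 days and is among those "that do not resolve within 4 weeks of reducing tamoxifen to 10 mg od".
- A thrombotic event of any grade.

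Section 13.4 (Trial Steering Committee) repeats the 7-of-21 figure and refers back to 12.4. It offers no wider definition.

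Section 7.4 (Dose Modifications) governs the reduction: "Dose reductions to 10 mg tamoxifen od are allowed, but not mandated, for patients that develop mild/moderate side effects (grades 1-2", with thrombotic events excepted. It adds: "Dose modifications are only permitted on an individual basis at the discretion of the Chief Investigator/Clinical Coordinator".

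Section 7.9 (Patient Withdrawal) allows treatment to end without a reduction. On the patient's side: "If a patient chooses to withdraw from treatment only, the patient should discontinue treatment". The investigator may also stop treatment when an event makes continuing inadvisable in his or her judgement. The same section has a list headed "Patients must stop study treatment in the event of", and its toxicity and thrombosis items are the ones that 12.4 uses for its count.

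**The concern.** The grade 1-2 item joins its two conditions with an 'and'. A patient who never went down to 10 mg cannot satisfy the second one, however long the event lasted and however clearly it was related. Two patients with the same persistent event, both of whom stop because of it, are then classified differently according to whether an optional, centrally agreed step was taken first.

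The wording appears to have been carried over from the mandatory-stop list in 7.9. There it makes sense, because it says when a patient has to come off the drug. A tolerability count asks a different question: who did come off because of the drug.

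Section 1.2.2 says toxicity criteria were added because tamoxifen had not been used in this disease or together with cytoreductive agents. The 7-of-21 count is the only numerical toxicity trigger in the plan. What is at stake is how soon the TSC looks at a cluster of low-grade stops.

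**Working it through.** **The plan's own figures.** The plan gives no target rate or error rate for 7 of 21, so there is nothing to reproduce for the trigger. The one calculated design figure, in 12.6, does reproduce. With 42 patients and 3 or more responders, the exact binomial tail is 0.0515 at 2% (limit 0.10) and 0.805 at 10% (target 0.80).

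**Who is counted when 12.4 is applied literally**

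| Reason for stopping | In the 21 | Can be in the 7 |
|---|---|---|
| Related grade 3-4 event | yes | yes |
| Thrombotic event, any grade | yes | yes |
| Related grade 1-2 event, over 14 days, unresolved within 4 weeks at 10 mg | yes | yes |
| Related grade 1-2 event, over 14 days, stopped without trying 10 mg | yes | no |

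**Effect without assuming any rate.** Let T be the number of the 21 who fall in any of the four rows, and d the number in the last row. The count under 12.4 is T - d. For T of 7 or more, the trigger is missed when T - d is 6 or less, that is, when d is at least T - 6. So d = 1 is enough if T = 7, d = 2 if T = 8, and d = 3 if T = 9.

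**Illustrative probabilities.** Let p be the proportion who stop for any reason in the table, and f the share of those stops in the last row. Both are assumptions; the documents give neither. The chance of triggering is P(X ≥ 7) for X binomial with n = 21 and probability p(1 - f).

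| p | f = 0 | f = 10% | f = 25% | f = 50% |
|---|---|---|---|---|
| 20% | 0.109 | 0.068 | 0.029 | 0.003 |
| 30% | 0.449 | 0.331 | 0.175 | 0.029 |
| 40% | 0.800 | 0.678 | 0.449 | 0.109 |

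The f = 0 column is the chance if every such stop counts. If f is small, the loss is small.

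**Delay if the trigger is missed.** Inputs are 42 patients over 28 months (Synopsis, Sample Size), TSC meetings every 6 months (13.4) and Trial Management Group (TMG) meetings every two months (13.3). Assuming even accrual, 42 / 28 = 1.5 registrations per month.

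- Worst case, to the next scheduled TSC meeting: 6 months, 6 × 1.5 = 9 registrations.
- Average, if timing is random within the TSC cycle: 3 months, 3 × 1.5 = 4.5 registrations.
- Longest wait for the next TMG meeting: 2 months, 2 × 1.5 = 3 registrations.

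**The case against.** The strongest defence is that the condition is deliberate. The trigger is about unacceptable toxicity and uses the same definition as the patient-level rule. A mild event abandoned at 20 mg does not show that tamoxifen cannot be tolerated when 10 mg was available, and the condition keeps manageable symptoms from weighing as much as a grade 3-4 event or a thrombosis. This would carry more weight if the reduction were required. Because it is optional and needs central agreement, the count depends on how a stop was handled as well as on what the patient experienced. The wish to keep mild stops apart from serious ones is fair, and presenting the count by grade meets it.

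Section 7.9 also names toxicity and patient choice as different reasons for stopping: "unacceptable toxicity or patient choice, full details of the reason/s for discontinuation should be recorded on the CRF". Not every withdrawal by choice hides a drug effect, and the documents do not show how many direct stops would be related, or that there would be any. This stands, and it is why no probability above can be read as an estimate.

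The 14-day condition is a separate filter, and nothing here argues against it. A patient who stops on day 3 with a grade 1 symptom should stay outside the count.

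Oversight does not depend on the trigger. "The independent Trial Steering Committee (TSC) will review all SAEs", the TSC may ask to meet more often, and 13.3 and 13.4 allow emergency meetings of the TMG and the TSC. This also stands, with one limit: persistent grade 1-2 stops need not be serious adverse events, so the review of serious events need not reveal them.

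**Conclusion.** The point holds as a gap in the definition and is minor. Followed exactly, 12.4 keeps a direct stop for a persistent related grade 1-2 event in the denominator and out of the count.

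A reader might infer more, and three such readings are not supported.

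- *Toxicity would go unmonitored, or a stopping rule is broken.* Section 1.2.2 does speak of stopping criteria, but 12.4 and 13.4 make the trigger a prompt for TSC review, and routine review continues whether or not it is met.
- *Serious toxicity is missed.* Related grade 3-4 events and thrombotic events of any grade count with no reduction step.
- *Review would be six months late.* That figure is the worst case. It assumes that nobody uses the extra or emergency meetings, although stopping reasons are due within 2 weeks (9.1).

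Patient-level stopping rules, the primary analysis and the reported safety outcomes are unaffected. Confidence is high in the reading of the text. The size of the effect is unknown: the T - 6 relation needs no rates, while every probability rests on assumed p and f, and the registration counts rest on even accrual.

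**What to change.** For the TSC trigger only, reword the grade 1-2 item in 12.4 along these lines: *a grade 1-2 adverse event considered related to tamoxifen, lasting more than 14 days, that leads to permanent discontinuation, whether or not 10 mg was tried*. Keep the items for related grade 3-4 events and thrombotic events, and keep 7 of 21. Leave 7.4 and 7.9 unchanged. Section 13.4 needs no edit because it points to 12.4.

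Show the TSC the count by grade and by whether 10 mg was tried, with thrombotic events on their own line.

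The cost is small but not nil. Date and reason for stopping are on the Treatment Discontinuation Form; grade and relatedness come from adverse event reporting, and dose from the treatment forms. These have to be linked, but all are already collected.

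The trigger will be met more often. At an assumed 20% intolerance with a quarter of stops uncounted, the probability rises from 0.03 to 0.11, nearly fourfold; with a tenth uncounted, it rises from 0.07 to 0.11. Each extra occurrence costs one TSC review. The plan gives no rationale for 7 of 21 that could be used to recalibrate it for the wider count, and for a trigger that only prompts a review, erring toward more review is acceptable.
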